### Recruitment and study scope

To achieve the planned sample size and enhance external validity, this study will be conducted as a multicenter trial. Spanish hospitals with specialized units in colorectal surgery, radiology, oncology, and radiotherapy will participate. Most centers belong to the TAUTEM study network [22].

Participating centers: 1. Parc Tauli University Hospital; 2. Mutua de Terrassa University Hospital; 3. Bellvitge University Hospital; 4. Joan XXIII University Hospital; 5. Vall d’Hebron University Hospital; 6. Hospital de San Juan Despí Moisès Broggi; 7. Santa Creu i Sant Pau University Hospital; 8. Donostia University Hospital: 9. Complejo Hospitalario Universitario Torrecárdenas; 10. Hospital Universitario Fundación Jiménez Díaz; 11. Hospital Clinic University Hospital; 12. La Fe University Hospital.

### Informed consent and legal considerations

The protocol, patient information, and informed consent forms will be approved by the Ethics Committees for Research with Medicinal Products (CEIm) of all participating centers. The trial is registered at ClinicalTrials.gov (ID: NCT06450574). All patients must sign the informed consent form prior to randomization.

The study will be conducted in accordance with current Spanish legislation, with authorization from the Spanish Agency for Medicines and Medical Devices (AEMPS), the 7th revision of the Declaration of Helsinki [29], the SPIRIT 2013 guidelines for clinical trials [30], and the CONSORT statement for randomized controlled studies [31].

All trial documentation (protocol and consent forms) will be processed through the CTIS (Clinical Trial Information System) portal for AEMPS authorization, in compliance with Royal Decree 1090/2015 [32]. The reference CEIm will be the CEIm Parc Taulí, which, along with AEMPS, will evaluate the methodological and clinical procedures of the trial and safeguard participant safety and welfare, reviewing all information provided to participants.

### Randomization

Patients who meet all inclusion criteria, none of the exclusion criteria, and have signed the informed consent form will be randomized. Allocation to the CRT–TEM or TEM group will be performed in a 1:1 ratio using a computer-generated randomization sequence implemented in the electronic Case Report Form (eCRF) centralized by the Contract Research Organization (CRO). The system will automatically assign treatment once eligibility criteria are confirmed.

### Study procedures (Fig. 1)

**Fig. 1 Fig1:**
[figure not shown]
CONSORT trial flow chart of the TAUTEM-T1 study. CRT, chemoradiotherapy; TEM, transanal endoscopic microsurgery; TME, total mesorectal excision; MRI, magnetic resonance imaging; ER, endorectal ultrasound; FCS, full colorectal study; QoL, quality of life; CEA, carcinoembryonic antigen; CA 19–9, carbohydrate antigen 19–9; EORTC, European Organisation for Research and Treatment of Cancer; LARS, low anterior resection syndrome

Before TEM surgery or initiation of CRT, all patients will complete validated quality-of-life questionnaires from the European Organization for Research and Treatment of Cancer (EORTC) [33]: EORTC QLQ-C30 (version 2) [34] and EORTC QLQ-CR29 (colorectal cancer–specific module) [35]. Anorectal function will also be assessed using the LARS score [6, 36] and the Wexner fecal incontinence questionnaire [37].

### Chemoradiotherapy-TEM group (CRT-TEM)

#### Neoadjuvant treatment: preoperative CRT (long-course regimen)

Neoadjuvant chemotherapy will be administered concomitantly with radiotherapy and will consist of oral capecitabine 825 mg/m^2^ every 12 h on radiotherapy days.

Long-course radiotherapy will be administered using one of the following techniques, depending on institutional availability, with preference for the first:Volumetric modulated arc therapy (VMAT). Two treatment fields will be defined. Primary (standard) field includes the tumor, the mesorectum, and the regional pelvic lymph nodes, delivering a total dose of 45 Gy in 25 fractions (1.80 Gy/fraction). For the elective pelvic CTV, the cranial border will be set at the S2–S3 junction to minimize toxicity in this cT1N0M0 population. Cranial extension up to the sacral promontory/common iliac bifurcation may be considered only when clinically indicated (e.g., higher tumor location or suspicious nodal disease). Boost field: includes the tumor area and any pathological adjacent lymph nodes, delivering a total dose of 50 Gy in 25 fractions (2.00 Gy/fraction). An integrated boost technique, inherent to VMAT, will be used [38].Conventional three-dimensional planning (3D-CRT). The same target volumes as in (1) will be treated but using a sequential boost: 45 Gy in 25 fractions to the primary field, followed by 5.40 Gy in 3 fractions to the boost field. This schedule results in 28 treatment sessions, with the same fractionation (1.80 Gy/fraction) [39, 40].

At week 9 after completion of CRT, clinical response will be assessed by pelvic MRI, endoscopic and digital rectal exam [41]. CRT-related adverse events will be prospectively recorded and graded according to CTCAE v5.0. Acute toxicity will be collected from CRT initiation through 30 days after TEM, and late toxicity will be collected thereafter during follow-up up to 3 years.

#### Local excision by transanal endoscopic surgery

Local excision will be performed using transanal endoscopic surgery at week 10 after neoadjuvant treatment (TEM [42], TEO [43], or TAMIS [44]) under general or spinal anesthesia. Preoperative preparation will include mechanical bowel cleansing, and antibiotic and thromboembolic prophylaxis.

To ensure reliable identification of the original tumor site at week 10—particularly in cases of marked regression—baseline lesion localization will be standardized and recorded using (i) distance from the anal verge to the distal tumor margin (rigid rectoscopy and/or endoscopy) and (ii) circumferential quadrant/clock-face position (anterior, posterior, right or left lateral), together with high-quality baseline endoscopic photo documentation. Tattooing with carbon/ink is not recommended, as diffusion may hinder subsequent identification of the residual scar.

The procedure will consist of full-thickness excision centered on the scar/original tumor site, even when only a subtle scar is visible, with a circumferential margin of approximately 20 mm around the scar (minimum 10 mm), without entering the perirectal fat [7].

### TEM group (TEM)

Patients assigned to the TEM group will undergo transanal endoscopic microsurgery, following the same local excision procedure described above.

### Pathological study

Histologic tumor regression after CRT will be evaluated according to the Bouzourene classification (GR1: no residual tumor—complete regression; GR2: isolated residual tumor glands; GR3: predominance of fibrosis over tumor; GR4: predominance of tumor over fibrosis; GR5: no tumor changes—absence of regression) [45] and/or the Dworak classification (GR0: no tumor changes—no regression; GR1: dominant tumor mass with fibrosis and/or vasculopathy, regression < 25%; GR2: predominance of fibrosis with few glandular clusters—26–50%; GR3: only occasional residual glands— > 50%; GR4: no residual tumor—complete regression) [46].

The pathological report of the local excision specimen will include: lesion size (maximum and minimum diameters, in mm), adenocarcinoma differentiation grade, degree of submucosal invasion, tumor regression grade (according to Bouzourene or Dworak), pathological stage (pT1, pT2, pT3), venous, lymphatic, or perineural invasion, tumor budding, and margin status (minimum distance in mm).

The degree of submucosal invasion will be determined using the Taulí-pT1 classification described by Casalots et al. [11], based on the residual healthy submucosa (hrSB); the percentage of invasion is calculated as: [(total submucosal thickness – hrSB)/total submucosal thickness)] × 100 [11, 13]. In case of diagnostic difficulties at participating centers, samples will be sent to the Pathology Service of Parc Taulí Hospital for centralized review.

### Definition of clinical and pathological response to preoperative chemoradiotherapy

At week 9 after completion of preoperative CRT, and prior to TEM, clinical response will be assessed using a multimodal approach, integrating digital rectal examination (DRE), endoscopy, and pelvic magnetic resonance imaging (MRI).

Clinical response will be categorized as complete, near-complete, or incomplete based on the combined findings of these assessments. Complete clinical response will be defined by the absence of palpable tumor on DRE, no visible residual lesion on endoscopy (flat scar with or without telangiectasia), and no evidence of residual tumor or suspicious lymph nodes on high-resolution MRI, including diffusion-weighted imaging. Incomplete response will be defined by the presence of residual tumor on clinical, endoscopic, or radiological evaluation [41].

Regardless of response category (complete, near-complete, or incomplete), patients who remain staged as cT1N0 on week-9 MRI restaging will proceed to protocol-mandated local excision at week 10. A watch-and-wait strategy is not permitted within the trial, as histopathologic assessment of the excision specimen is required to guide the predefined escalation algorithm.

Pathological response will be classified according to Bouzourene or Dworak: pCR, Bouzourene GR1 or Dworak GR4; pPR, Bouzourene GR2–GR3 or Dworak GR2–GR3; and absence of pathological response, Bouzourene GR4–GR5 or Dworak GR0–GR1.

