#### Secondary variables

CRT-related adverse events will be prospectively recorded and graded according to CTCAE v5.0 [47]. Acute toxicity will be collected from CRT initiation through 30 days after TEM, and late toxicity will be collected thereafter during follow-up up to 3 years.

*Quality-of-life outcomes* will be assessed using the EORTC QLQ-C30, EORTC QLQ-CR29, Wexner, and LARS questionnaires before surgery and at 12 months. Clinical response to CRT will be evaluated using the predefined multimodal clinical assessment.

*Demographic variables:* age, sex, and recruiting hospital.

*Preoperative or pre-neoadjuvant phase:* Baseline tumor characteristics will include tumor size (measured by colonoscopy, endorectal ultrasound [ER], and pelvic MRI; maximum diameter in mm), distance from the anal verge, tumor location (anterior, posterior, right or left lateral), percentage of rectal circumference involved, ER and MRI staging, presence of distant metastases (thoracoabdominal CT), preoperative tumor markers (CEA and CA 19–9), and histological grade on biopsy. After completion of neoadjuvant chemoradiotherapy and prior to local excision, clinical response will be assessed using a multimodal approach integrating digital rectal examination, endoscopy, and pelvic MRI, and will be categorized as complete, near-complete, or incomplete clinical response, according to predefined criteria.

*Surgical variables*: the technique employed, operative time, estimated blood loss, intraoperative complications, conversion to abdominal surgery, en bloc resection, and closure of the defect.

*Pathological variables*: tumor size, differentiation grade, response grade to CRT, pT stage, venous, lymphatic, or perineural invasion, tumor budding, local excision specimen margins (minimum lateral and deep distances, in mm), presence of muscularis propria, residual healthy submucosa/submucosal invasion, and sm classification according to Taulí-pT1.

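### The printed Dworak bands conflict with their own wording, and because either regression scale may be used, the partial versus no-response split can depend on the centre

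*Protocol article*

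**What the plan says.** The Pathological study section of the protocol article sets out two regression scales joined by and/or, and says that the specimen report may use either.

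- Bouzourene is defined in words only. The better grades are "GR1: no residual tumor—complete regression; GR2: isolated residual tumor glands; GR3: predominance of fibrosis over tumor", and the poorer ones are "GR4: predominance of tumor over fibrosis; GR5: no tumor changes—absence of regression".
- Dworak is defined in words and in percentages. The poorer grades are "GR0: no tumor changes—no regression; GR1: dominant tumor mass with fibrosis and/or vasculopathy, regression < 25" per cent. The middle grade is "GR2: predominance of fibrosis with few glandular clusters—26–50" per cent. The better grades are "GR3: only occasional residual glands— > 50%; GR4: no residual tumor—complete regression".

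The section defining clinical and pathological response then turns grades into categories. Complete response is Bouzourene GR1 or Dworak GR4, and the rest follow: "pPR, Bouzourene GR2–GR3 or Dworak GR2–GR3; and absence of pathological response, Bouzourene GR4–GR5 or Dworak GR0–GR1".

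Neither section says which scale decides if both are reported and differ, or whether the words or the percentages decide a Dworak grade. Central pathology review is offered only where a centre meets diagnostic difficulty. Evaluating the pathological response to chemoradiotherapy is a stated secondary objective.

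**The concern.** A response category should depend on the specimen and not on the classification the local pathologist prefers. Here two centres can both follow the protocol and report the same specimen differently, because the words and the figures printed for Dworak do not describe the same grades. Words and figures part at the boundary between partial response and no response.

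What is at stake is the interpretability of one secondary outcome in one arm. Each centre contributes only some of the CRT–TEM specimens, so a difference in scale would be mixed with any real difference between centres and could not be separated afterwards. Central review would not catch this: a pathologist who applies the printed bands has no diagnostic difficulty and no reason to refer the slides.

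**Working it through.** The plan gives no figure to reproduce. The check compares definitions, first by words and then by percentages. All inputs are the grade definitions and the category rule set out above.

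**Step 1: match the grades by their words.** The scales run in opposite directions, so Bouzourene grade *b* should pair with Dworak grade 5 − *b*.

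| Bouzourene | Dworak (5 − *b*) | Shared meaning | Category, Bouzourene | Category, Dworak |
|---|---|---|---|---|
| 1 | 4 | no tumour left | complete | complete |
| 2 | 3 | a few scattered glands | partial | partial |
| 3 | 2 | mostly fibrosis | partial | partial |
| 4 | 1 | mostly tumour | none | none |
| 5 | 0 | unchanged | none | none |

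All five pairs agree. By wording, the category rule is a correct reversal.

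**Step 2: read Dworak by its percentages.** GR1 states that its percentage is regression. The protocol does not say how regression is measured, so an assumption is needed: let *r* be the fibrosis share of the lesion, in per cent. Fibrosis then predominates when *r* > 50, tumour predominates when *r* < 50, and neither does at *r* = 50.

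| *r* (%) | Dworak by percentage | Category | Bouzourene by words | Category | Agree? |
|---|---|---|---|---|---|
| 0 | 0 | none | 5 | none | yes |
| above 0, below 25 | 1 | none | 4 | none | yes |
| 25 | no grade | undefined | 4 | none | undefined |
| 26–49 | 2 | partial | 4 | none | **no** |
| 50 | 2 | partial | neither predominates | unclear | unclear |
| above 50, below 100 | 3 | partial | 2 or 3 | partial | yes |
| 100 | 4 | complete | 1 | complete | yes |

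The 26–49 row is the conflict. Dworak GR2 by its figure is a partial response, while Bouzourene "GR4: predominance of tumor over fibrosis" is no response.

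**Step 3: look within Dworak alone.** At *r* = 40, for example, 60% of the lesion is tumour. By figure the grade is GR2, a partial response. By words it fits GR1, where tumour is dominant, and that is no response. A centre that uses only Dworak therefore meets the same ambiguity.

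**Step 4: other faults in the bands.** GR1 stops below 25 and GR2 starts at 26, so a value of exactly 25, or any fraction between 25 and 26, has no grade. GR3 pairs occasional glands with anything above 50%. At *r* = 55, 45% of the lesion is still tumour, yet the figure gives GR3. That mismatch does not change the category, because GR2 and GR3 are both partial responses.

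**The case against.** The strongest defence is that the grades are defined by their words, and that by their words the two scales match perfectly. On that view the percentages are loose annotations and the 26–49% conflict exists only under an assumption about what they measure. The first part is right, as Step 1 shows. The assumption is also not stated in the protocol. But the percentages are printed as part of the grade definitions with nothing to say that they yield to the words, so a pathologist who uses them is following the protocol.

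Several stronger readings are tempting, and the documents do not support them.

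- *The category rule maps the scales inconsistently.* A reader might infer this from GR2–GR3 appearing for both scales. It appears twice because it is the middle range of each.
- *Opposite direction is itself an error.* The category rule and the exit criteria name the scale beside each grade. The variable list ("tumor size, differentiation grade, response grade to CRT, pT stage") does not name it, but it is a short list in a condensed article and the eCRF is not shown. It does not show that a grade will be stored without its scale.
- *The complete-response rate, and the later watch-and-wait trial that rests on it, is at risk.* Both scales define complete response as no residual tumour. One miscoded specimen would move the rate by 1/53 = 1.9 percentage points, but that would be a transcription error and not a consequence of the plan.
- *About 24 patients are affected.* With 53 CRT–TEM patients and a complete-response rate of 55%, 53 × 0.45 = 23.9 would lack a complete response. That counts every such patient, not those in the 26–49% band. It also assumes that all 53 have an excision specimen, whereas patients upstaged on MRI go to TME without local excision.

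It also stands that the outcome is secondary and assessed in one arm, so no between-arm comparison depends on it. The exit criteria say that absence of pathological response alone does not require completion TME.

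**Conclusion.** The point holds in a limited form. The printed Dworak definition contradicts itself at GR2 and leaves 25% ungraded. Two scales are allowed without a rule of precedence. If regression percentage means fibrosis share, specimens with about 26–49% regression are partial responses by the Dworak figure and non-responses by Bouzourene, or by Dworak's own words. The partial versus no-response split in the CRT–TEM arm can therefore depend on the centre.

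The size in patients cannot be stated, because the documents give no distribution of regression among incomplete responders. The primary endpoint, the complete-response rate and the completion-TME rule are not directly changed. This is more than detail left to an analysis plan: the protocol itself fixes the grades, bands and categories, and they conflict. It should be corrected, but it does not threaten the trial's main conclusion.

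**What to change.** In the Pathological study section and in the section defining pathological response, name one regression scale for the response endpoint at all centres. Define complete, partial and no response on that scale only. If Dworak is kept, reconcile the GR2 wording with its percentage, say whether words or percentages govern, and close the gap between 25% and 26%. If a centre also reports the other scale, record it in a separate, named field that does not enter the endpoint.

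The cost is a rewording of two sections and, where needed, one extra data field. Some centres will have to report on a scale that they do not routinely use. Sample size, treatment and follow-up are unaffected.

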### Criteria for exiting the study protocol

The study protocol will be discontinued and patients will proceed to standard radical surgery with TME in the following pre-excision situations: (i) local excision is not performed using standard transanal endoscopic surgery techniques (TEM, TEO, or TAMIS) or requires conversion to abdominal surgery; or (ii) at week 9 after completion of neoadjuvant therapy, pelvic MRI restaging shows ≥ cT2 and/or cN1 (any T) [41].

Patients who do not complete neoadjuvant therapy due to toxicity, intolerance, or personal decision, and patients with an incomplete clinical response at week 9 without MRI upstaging, will still proceed to local excision (TEM/TEO/TAMIS) as per protocol; treatment modifications and response category will be recorded for secondary analyses.

Following the pathological report of the local excision specimen, the protocol will be terminated and completion TME will be indicated if any of the following are present: adverse prognostic factors (grade G3, venous, lymphatic, or perineural invasion, or tumor budding); absence of the muscularis propria layer preventing evaluation of submucosal invasion; surgical margin (lateral or deep) < 1 mm; submucosal invasion classified as sm3 according to the Taulí-pT1 classification; or pathological stage higher than pT1 or ypT1.

Absence of pathological response to CRT (Bouzourene GR4–GR5 or Dworak GR0–GR1) alone, in the setting of a pT1/ypT1 lesion with clear margins and no adverse features, will not mandate completion TME and patients will continue standard surveillance. Completion TME will be performed within 4–6 weeks according to institutional guidelines and protocols.

### Follow-up (Fig. 1)

In both groups, quality-of-life and bowel dysfunction questionnaires (EORTC QLQ-C30, EORTC QLQ-CR29, LARS, and Wexner) will be administered 12 months after surgery. For patients with a protective stoma, these assessments will be performed 12 months after stoma closure.

During the first three years, digital rectal examination and rectosigmoidoscopy with multifocal biopsies of the scar will be performed every 4 months. If any biopsy is positive for adenocarcinoma or if clinical findings are suspicious, extension studies will be completed with endorectal ultrasound (ER) and/or pelvic MRI. Tumor markers (CEA and CA 19–9) will be measured every 4 months. In addition, abdominopelvic CT and chest X-ray will be performed annually (up to 3 years). A total colonoscopy will be scheduled 1 year after surgery and, if normal, subsequent surveillance will follow each center’s institutional protocol.

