## Introduction

Management of early rectal cancer (stage I: T1–T2, N0, M0) varies widely. For T1N0M0 tumors without adverse pathological factors, local excision (LE) is the standard treatment per international guidelines [1, 2]. However, in T1 lesions with adverse features and in T2 tumors, lymph node involvement may reach 12–28%, warranting total mesorectal excision (TME) [3].

TME, described by Heald, markedly reduced local and systemic recurrence in rectal cancer [4]. However, it is associated with substantial morbidity, including temporary/permanent stomas and relevant mortality, as well as long-term functional sequelae such as genitourinary dysfunction and low anterior resection syndrome (LARS) [5, 6]. In appropriately selected patients, transanal endoscopic local excision (LE) preserves the rectum and is associated with lower morbidity and minimal sphincter/genitourinary impairment [7, 8]. Nonetheless, despite a generally favorable prognosis in stage I disease, standard management does not typically include neoadjuvant therapy [9].

pT1 rectal adenocarcinomas can be classified into two groups according to surgical and histological criteria: (1) favorable prognosis tumors, with a local recurrence risk < 5%; and (2) unfavorable prognosis tumors, with a local recurrence risk up to 29% [10]. Favorable surgical factors include en bloc resection, full-thickness excision, and clear margins > 1 mm. Unfavorable histopathologic factors associated with nodal involvement include depth of submucosal invasion, poor differentiation, venous/lymphatic or perineural invasion, positive margins (< 1 mm), and tumor budding [2, 8]. Depth of submucosal invasion is the main determinant of nodal risk [3], as most other adverse factors occur in < 10% of pT1 cases [1]. Its prognostic value has been questioned by the meta-analysis by Zwager et al. [12], although several included studies had methodological limitations.

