An initial proposal of our group when designing this protocol was to apply preoperative CRT followed by TEM in pT1N0M0 rectal tumors with adverse prognostic factors. The main limitation, however, is that these factors can only be identified after the pathological examination of the LE specimen. Preoperative biopsy merely confirms that the lesion is an infiltrating adenocarcinoma, and the only identifiable adverse feature is poor differentiation, present in less than 10% of cases [11, 14]. Therefore, it is not possible to reliably identify high-risk pT1N0M0 patients preoperatively. Moreover, as previously mentioned, in pT1N0M0 tumors without adverse features, LR exceeds 15–20% [11, 14], more than twice that observed in pT2–3abN0M0 cases from the TAUTEM study treated with neoadjuvant therapy and TEM (LR 7.4%) [22]. Hence, our hypothesis is to treat clinically staged T1N0M0 (cT1N0M0) rectal adenocarcinomas with preoperative CRT to reduce LR below that observed in the TAUTEM trial and increase rectal preservation [22, 23].

Primary objective. To evaluate whether preoperative CRT followed by transanal endoscopic microsurgery (CRT–TEM) increases rectal preservation at 3 years in patients with T1N0M0 rectal cancer without compromising oncologic outcomes, taking into account that local recurrences will be managed with TME, and that, after pathological examination of the specimen, cases presenting surgical or pathological adverse features or with upstaging to ≥ pT2 will also require completion TME according to protocol. Therefore, the challenge is to minimize the number of TMEs, given their well-documented surgical morbidity and functional impairment.

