### Secondary objectives

To assess the tolerance and adverse effects (acute and chronic) of preoperative chemoradiotherapy (CRT) in the CRT–TEM group (patient safety). To analyze postoperative morbidity and mortality in both groups (surgical outcomes). To evaluate clinical and pathological responses to CRT. To assess quality of life at 1 year after surgery in both groups. To compare long-term oncologic outcomes between groups (at 3 years): LR, DR, DFS, OS and rectal cancer–specific survival at 3 years.

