### Study variables

#### Primary variable (endpoint)

Difference in rectal preservation rate between CRT–TEM and TEM at 3 years after surgery. The database will be locked after all randomized patients have completed a minimum of 3 years of follow-up for the primary endpoint assessment.

Rectal preservation failure is defined as any completion TME due to protocol discontinuation criteria (e.g., adverse pathology or inadequate response) and/or any salvage TME performed for local recurrence during follow-up.

Local recurrence will be considered a rectal preservation failure irrespective of the subsequent management strategy (including cases treated without TME). Any TME performed for any reason during the 3-year follow-up (including postoperative complications, patient preference, or conversion to abdominal surgery resulting in TME) will be classified as rectal preservation failure. A temporary diverting stoma does not constitute rectal preservation failure; however, a permanent stoma at 3 years (even in the absence of TME) will be classified as rectal preservation failure. Death before 3 years and losses to follow-up will be handled under the ITT framework; in the primary analysis, patients without documented rectal preservation status at 3 years will be conservatively counted as failures, with sensitivity analyses using alternative assumptions. Patients who do not undergo TME for any reason but have persistent/uncontrolled primary disease will be counted as rectal preservation (rectum in situ) but will be recorded as local failure and as non–disease-free (DFS event).

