Pelvic CRT may impair bowel/anorectal function (e.g., urgency, frequency, incontinence and LARS), potentially offsetting organ-preservation benefits; therefore, function and QoL will be prospectively assessed using validated questionnaires (EORTC QLQ-C30/CR29, LARS and Wexner) at baseline and at 12 months (or 12 months after stoma closure).

Two alternative strategies may also be considered in cT1N0M0 disease. First, local excision with adjuvant (chemo)radiotherapy reserved for unfavorable pathology could reduce upfront CRT exposure; however, published evidence of (chemo)radiotherapy after local excision is associated with higher local recurrence rates than completion TME, particularly in pT1-2N0 disease, and may therefore represent a suboptimal rescue pathway when occult ≥ pT2 is identified [50, 51]. Second, a response-adapted approach randomizing complete/near-complete responders after CRT to watch-and-wait versus local excision is clinically appealing but requires robust evidence on pathological complete response rates and the safety of deferring surgery in cT1N0M0 tumors. TAUTEM-T1 is designed to generate this foundational evidence under standardized full-thickness excision and pathology review; if a high pCR rate and durable organ preservation are confirmed, a subsequent trial incorporating a watch-and-wait strategy in selected responders would be justified.

To our knowledge, no phase III multicenter randomized trial has specifically compared neoadjuvant therapy plus local excision versus standard TEM in T1N0M0 rectal cancer. Although earlier phase II studies in broader stages reported feasibility of organ preservation after neoadjuvant therapy, they did not focus on T1 disease and did not include a dedicated TEM comparator arm [52]. TAUTEM-T1 addresses this evidence gap using a superiority design and a patient-centered primary endpoint (rectal preservation), closely linked to functional outcomes and quality of life.

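### Moving all four questionnaires to 12 months after closure of a protective stoma ties the only post-baseline quality-of-life measurement to an event expected more often in the TEM arm

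*Protocol article*

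**What the plan says.** The secondary objective is "To assess quality of life at 1 year after surgery in both groups". The Secondary variables section lists the EORTC QLQ-C30, EORTC QLQ-CR29, Wexner and LARS "questionnaires before surgery and at 12 months", without exception.

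The Follow-up section gives the general rule for both groups, that the four questionnaires "will be administered 12 months after surgery", and then the exception: "For patients with a protective stoma, these assessments will be performed 12 months after stoma closure". The Discussion repeats the two-part timing: "at baseline and at 12 months (or 12 months after stoma closure").

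Besides baseline, no other questionnaire round is scheduled. The article does not say what happens when a protective stoma is not closed. The primary endpoint section does foresee that a stoma may remain: "a permanent stoma at 3 years (even in the absence of TME) will be classified as rectal preservation failure". It treats a temporary diverting stoma differently, as no failure.

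**The concern.** The Introduction links stomas to TME: "it is associated with substantial morbidity, including temporary/permanent stomas and relevant mortality". Any TME within 3 years is a failure of the primary endpoint. The stoma exception is therefore triggered by something that happens after randomisation, is closely related to the primary outcome, and is planned to be more frequent in one arm.

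Three things follow.

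- Patients with a protective stoma are measured later than the others and after a year of recovery from closure, so the arms are compared on two clocks.
- Because there is only one post-baseline round, their quality of life with the stoma in place is never recorded.
- A protective stoma that stays open never reaches its assessment date.

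The Discussion relies on these questionnaires to check whether CRT-related bowel impairment offsets the gain from organ preservation. Patients who keep the rectum are measured at 12 months, when CRT effects count in full. Patients who have a TME with a protective stoma are measured only a year after closure. Later analysis cannot recover questionnaires that were never given.

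**Working it through.** **1. The sections side by side.**

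| Section | Timing | Stoma exception |
|---|---|---|
| Secondary objectives | 1 year after surgery, both groups | none |
| Secondary variables | before surgery and 12 months | none |
| Follow-up | 12 months after surgery | protective stoma: 12 months after closure |
| Discussion | baseline and 12 months | 12 months after closure |

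Under the last two rows, a patient whose protective stoma is closed has no 1-year value, which the first two rows promise.

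**2. The plan's own figure.** The Sample size section gives 0.60 (TEM) and 0.85 (CRT-TEM), two-sided α = 0.05, power 80%, 53 per group and 106 in total with 10% dropout. With unpooled variance:

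n = (1.960 + 0.842)² × (0.60×0.40 + 0.85×0.15) / 0.25² = 46.2, rounded up to 47 per group

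47 / 0.90 = 52.2, rounded up to 53 per group, or 106 in total.

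The figure reproduces, with dropout already included in the 53. It serves here only to size the affected group; the documents give no figure for the quality-of-life endpoint.

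**3. Planned preservation failures at 3 years.**

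- TEM: 53 × 0.40 = 21.2
- CRT-TEM: 53 × 0.15 = 7.95
- Difference: 25 percentage points

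Many TEM-arm failures should come early. The Sample size section cites sm3 in 35-40% and adverse pathological factors in 5-10% of T1 tumours, and the exit criteria place completion TME within 4-6 weeks. The article does not split the 40% into early and late failures.

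**4. Patients deferred.** Assume that 30-90% of failures receive a protective stoma (not in the documents).

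- TEM: 21.2 × 0.30 = 6.4 to 21.2 × 0.90 = 19.1
- CRT-TEM: 7.95 × 0.30 = 2.4 to 7.95 × 0.90 = 7.2

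**5. Patients with no assessment time.** Assume further that 5-20% of these stomas are never closed (not in the documents).

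- TEM: 6.4 × 0.05 = 0.3 to 19.1 × 0.20 = 3.8
- CRT-TEM: 2.4 × 0.05 = 0.1 to 7.2 × 0.20 = 1.4

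**6. Shift in the between-arm mean.** Let s be the share of failures with a stoma and D the points lost on a 0-100 scale while it is in place (assumed 5-20). Suppose that the loss is present at 12 months and gone at the deferred assessment. Then

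shift = (0.40 − 0.15) × s × D

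| s | D = 5 | D = 10 | D = 20 |
|---|---|---|---|
| 0.30 | 0.4 | 0.8 | 1.5 |
| 0.50 | 0.6 | 1.3 | 2.5 |
| 0.70 | 0.9 | 1.8 | 3.5 |
| 0.90 | 1.1 | 2.3 | 4.5 |

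The TEM mean is raised more than the CRT-TEM mean, so the shift is against CRT-TEM in every cell.

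For given s and D these are upper bounds. The 40% and 15% are 3-year rates, and a salvage TME after month 12 does not alter a questionnaire already completed. Failure also includes recurrence managed without TME, a permanent stoma without TME and undocumented status. A stoma closed well before month 12 would cost less than D at that time.

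**The case against.** The strongest reply is that the exception is deliberate, is stated twice, and suits LARS and Wexner, which depend on bowel continuity. That stands for those two instruments. It does not carry over to QLQ-C30, a general quality-of-life questionnaire, or to QLQ-CR29 as a whole, and the Follow-up section does not separate them.

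A reader might infer that patients with a permanent stoma get no assessment. The text does not say so. The exception names only a protective stoma, so a stoma that is permanent from the start stays under the 12-month rule for both groups. The gap is confined to protective stomas that are never closed, probably a few patients.

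A reader might also infer that the comparison leaves out the burden that CRT is meant to avoid. The Introduction describes that aim thus: "the challenge is to minimize the number of TMEs, given their well-documented surgical morbidity and functional impairment". TME patients without a protective stoma are assessed on time. Those with a closed stoma complete all four questionnaires a year later, when lasting dysfunction shows. Morbidity after any completion or salvage TME is recorded at 30 and 60 days. What is lost is the stoma period and the common clock.

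Nor should deferred patients be counted as dropped: they still contribute a score, only later.

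Finally, the endpoint is secondary and the likely bias runs against CRT-TEM, so the rule is unlikely to create a favourable result for the experimental arm. That limits the harm, but the comparison is still distorted. Handling of a never-closed stoma could be left to a fuller document; the schedule that creates the problem is fixed in this article.

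**Conclusion.** The point holds in this limited form. For patients with a protective stoma, the only post-baseline quality-of-life measurement is timed by a post-randomisation event that the plan's own rates make more likely under TEM. The stoma period goes unmeasured, a never-closed protective stoma has no assessment time, and the comparison does not match the 1-year objective.

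The likely direction is against CRT-TEM. The size is uncertain: about 0.4-4.5 points on a 0-100 scale, as an upper bound, resting on assumed stoma shares of 30-90% and assumed losses of 5-20 points, neither of which is in the documents. The primary endpoint is unaffected. The change should be made, because the schedule cannot be repaired at analysis.

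**What to change.** 1. Give QLQ-C30 and QLQ-CR29 to every patient at the existing visit 12 months after the first trial operation, whatever the stoma status, and base the between-arm quality-of-life comparison on these. Naming the first operation also fixes the time origin for patients who later have a TME.
2. Keep the assessment 12 months after stoma closure as an addition, chiefly for LARS and Wexner.
3. Report by arm how many patients cannot be assessed on LARS and Wexner because of a stoma, including protective stomas never closed.
4. Align Secondary objectives, Follow-up, Secondary variables and the Discussion on this timing.

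The cost is one extra questionnaire set for stoma patients and a change of wording. Visits every 4 months are already planned, so no new visit or procedure is needed. A single 12-month round still does not describe stomas closed before, or formed after, that date, but it puts both arms on the same clock.
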